## Abstract

**Background:**

Whole brain radiation therapy (WBRT) is the standard therapy for multiple brain metastases. However, WBRT has a poor local tumor control and is associated with a decline in neurocognitive function (NCF). Aim of this trial is to assess the efficacy and safety of a new treatment method, the WBRT with hippocampus avoidance (HA) combined with the simultaneous integrated boost (SIB) on metastases/resection cavities (HA-WBRT+SIB).

**Methods:**

This is a prospective, randomized, two-arm phase II multicenter trial comparing the impact of HA on NCF after HA-WBRT+SIB versus WBRT+SIB in patients with multiple brain metastases. The study design is double-blinded. One hundred thirty two patients are to be randomized with a 1:1 allocation ratio. Patients between 18 and 80 years old are recruited, with at least 4 brain metastases of solid tumors and at least one, but not exceeding 10 metastases ≥5 mm. Patients must be in good physical condition and have no metastases/resection cavities in or within 7 mm of the hippocampus. Patients with dementia, meningeal disease, cerebral lymphomas, germ cell tumors, or small cell carcinomas are excluded. Previous irradiation and resection of metastases, as well as the number and size of metastases to be boosted have to comply with certain restrictions. Patients are randomized between the two treatment arms: HA-WBRT+SIB and WBRT+SIB. WBRT is to be performed with 30 Gy in 12 daily fractions and the SIB with 51 Gy/42 Gy in 12 daily fractions on 95% of volume for metastases/resection cavities. In the experimental arm, the dose to the hippocampi is restricted to 9 Gy in 98% of the volume and 17Gy in 2% of the volume. NCF testing is scheduled before WBRT, after 3 (primary endpoint), 9, 18 months and yearly thereafter. Clinical and imaging follow-ups are performed 6 and 12 weeks after WBRT, after 3, 9, 18 months and yearly thereafter.

**Discussion:**

This is a protocol of a randomized phase II trial designed to test a new strategy of WBRT for preventing cognitive decline and increasing tumor control in patients with multiple brain metastases.

**Trial registration:**

The HIPPORAD trial is registered with the German Clinical Trials Registry (DRKS00004598, registered 2 June 2016).

## Background

Brain metastases are the most common intracranial tumors in adults, occurring in 10–30% of patients with systemic malignancies [1]. For patients with multiple brain metastases, whole brain radiation therapy (WBRT) remains the primary treatment modality [2].

WBRT was shown to significantly improve distant intracerebral tumor control and reduce the rate of neurological death compared to radiosurgery alone [3], leading to the assumption of relevant microscopic tumor infiltration of the brain. Consequently, the whole brain can be considered a clinical target volume (CTV) and would benefit from a moderate radiation dose [3].

However, WBRT is associated with long-term side effects. Patients receiving additional WBRT after local therapy reported significantly poorer quality of life (QoL) scores than patients receiving local therapy only [4]. The differences were clinically relevant as early as 8 weeks after treatment. The main culprit are neurocognitive deficits frequently observed after WBRT of multiple brain metastases, with episodic memory being the predominant cognitive domain affected [5–7]. Memory deficits are correlated with and precede decreased quality of life [8], and thus play an essential role in patients’ subjective well-being. Although other factors contribute to memory decline, such as age, tumor growth or medication, WBRT has clearly been demonstrated to significantly impair memory [5, 9].

The hippocampus is the human brain structure that is most critically involved in episodic memory processing [10, 11]. Damage to the hippocampi can lead to profound amnestic syndromes [12]. It has been demonstrated that a reduction of adult neurogenesis within the hippocampus leads to hippocampal dysfunction [13, 14] and that irradiation blocks adult neurogenesis in the subgranular zone of the hippocampus [15]. Episodic memory deficits after WBRT have therefore been concluded to be associated with hippocampal damage [16, 17]. Hippocampal damage might be prevented by hippocampus avoidance-WBRT (HA-WBRT), which is hypothesized to attenuate cognitive decline as measured by standardized neuropsychological testing. Results of the RTOG 0933, a single-arm non-randomized phase II trial of conformal HA during WBRT, showed a preservation of memory and QoL compared to a historical series of patients receiving standard WBRT [18]. The NRG Oncology CC001 phase III randomized trial investigating WBRT and memantine hydrochloride versus HA-WBRT and memantine hydrochloride recently showed a significantly higher risk of neurocognitive failure in the conventional WBRT arm [19]. The avoidance of the hippocampus during WBRT is considered to be a safe treatment concept, with a rate of (peri)hippocampal disease progression after HA-WBRT according to previous data between 7.6 and 12.1% [20–22].

Apart from the HA-WBRT, the current trial plans an additional boost to the metastases with the aim of obtaining an improved local tumor control (LTC). Progressive brain metastases have been correlated with significant neurocognitive deterioration [23–25], suggesting that LTC can have an essential contribution to the preservation of cognitive functions. In our pilot cohort, the LTC of boosted metastases and the intracranial progression-free survival (PFS) were significantly higher after HA-WBRT+SIB compared to conventional WBRT, emphasizing the potential benefit of intensified local treatment even for patients with more than 4 brain metastases [22]. The dose escalation in the form of sequential radiosurgeries after WBRT was also previously investigated by Andrews et al. and showed improved LTC and overall survival (OS) rates [26].

In the preparation of this clinical trial protocol, a planning study was performed, in search for the best state-of-the-art radiotherapy technique to safely apply the required dose, while providing optimal HA [27]. Both a simultaneous integrated boost (SIB) and a sequential approach were investigated and both were able to achieve adequate whole brain coverage and radiosurgery-equivalent dose distributions to individual brain metastases. The SIB technique however achieved better sparing of the hippocampi, especially when a hippocampal avoidance region > 5 mm was used. Consequently, this approach is used in the context of this trial.

Thus, the current project aims to prospectively investigate the benefits of the novel, recently established technique of HA-WBRT+SIB in comparison to WBRT+SIB without HA on the memory performance of patients treated for brain metastases. The main hypothesis of this study is that HA-WBRT+SIB minimizes the side effect of cognitive deterioration and shows similar efficacy with regard to LTC and survival as compared to WBRT+SIB. Moreover, the study will assess safety, as well as structural and functional changes of the brain using magnetic resonance imaging (MRI).

## Methods

### Trial design and setting

This is a prospective, randomized, two-arm phase II multicenter trial comparing the impact of hippocampal sparing on the neurocognitive function (NCF) during HA-WBRT+SIB versus WBRT+SIB in patients with at least 4 brain metastases. The study design is double-blinded, with patients and assessors of NCF and MRI blinded to the assigned treatment arm. One hundred thirty two patients are to be randomized with a 1:1 allocation ratio to the treatment arms. Due to the anticipated loss during the screening period, we expect that 160 patients will have to be screened for enrolment.

Trial sites are academic hospitals and community clinics located in Germany and Switzerland: Bad Saarow, Dresden (two sites), Dessau, Freiburg, Frankfurt (two sites), Hamburg, Hameln, Kiel, Cologne, Moenchengladbach, Munich (two sites), Regensburg, Wolfsburg, Wuerzburg, Tuebingen, Zurich (two sites).

The trial and its amendments (current version: V.3.0 / 27.08.2018) were approved by the ethics committee of the University of Freiburg (EK-Freiburg 108/16) and by the local ethics committees of participating sites. The trial is associated with the German Cancer Society Neuro-Oncology Working Group NOA (Neuroonkologische Arbeitsgemeinschaft, NOA-14), the Radiation Oncology Group (Arbeitsgemeinschaft Radiologische Onkologie, ARO 2015–3) of the German Cancer Society (Deutsche Krebsgesellschaft, DKG) and the Radiation Oncology Group of the German Cancer Consortium (DKTK-ROG) and is funded by the German Cancer Aid (Deutsche Krebshilfe, Grant No. 110912).

### Study population

The target population for this trial consists in patients with at least 4 brain metastases of solid tumors, with at least one, but not exceeding 10 metastases ≥5 mm (i.e., eligible for dose escalation). No gender ratio has been stipulated in this study as the results of the preclinical and/or clinical studies did not indicate any difference in the effect of the study treatment in terms of efficacy and safety. However, patients over the age of 80 are excluded, as NCF tests have not been validated for older age cohorts.

Inclusion criteria to be met at the time of registration/randomisation are:
Patient’s written informed consent obtained,Age 18–80 years, male or female,Legal capacity, patient is able to understand the nature, significance, and consequences of the trial,At least 4 brain metastases of solid tumors, with at least one, but not exceeding 10 metastases ≥5 mm (i.e., eligible for dose escalation),Recursive partitioning analysis classification I or II,No metastases (either pre-irradiated or not) and no resection cavity within the hippocampus or in a distance of 7 mm to the hippocampus (= hippocampal avoidance region, HAR).

Exclusion criteria are:
Simultaneous participation in other interventional trials which could interfere with this trial,Participation in a clinical trial within the last thirty days before the start of this trial, previous participation (randomization) in this trial,Known or persistent abuse of medication, drugs or alcohol,Persons who are in a relationship of dependence/employment with the sponsor or the investigator,Pregnancy, nursing or patient not willing to prevent a pregnancy during treatment,Cerebral lymphomas, metastases of germ cell tumors, small cell lung cancer,Acute neurological symptoms demanding an immediate start of radiation therapy,Central nervous system diseases or syndromes accompanied by cognitive deficits or radiological changes of the brain, e.g., dementia (VLMT-Learning < 39; VLMT-Delayed Recall < 7), major depression, clinically manifest hypertensive encephalopathy, carcinomatous meningitis,Previous brain irradiation (radiosurgery/stereotactic fractionated radiotherapy (SFRT)) of > 1 brain metastasis > 3 cm or > 3 brain metastases > 1 cm each,Previous brain irradiation < 3 months before start of treatment,Previous surgical resection (± adjuvant SFRT) of > 1 brain metastasis (biopsy allowed),Previous surgical resection of 1 brain metastasis < 4 weeks before start of treatment,Uncontrolled pretreated brain metastasis/−es after radiosurgery/SFRT,Last application of chemotherapy/ immunotherapy/ targeted therapy < 1 week before randomization,Radiotherapy planning conforming to organ at risk (OAR) constraints not feasible (including previous cranial irradiation),Benzodiazepines, barbiturates, topiramate, hydantoine as antiepileptic medication,More than 1 brainstem metastasis ≥5 mm,Brainstem metastasis > 2 cm,Brain metastasis > 3.5 cm,Resection cavity eligible for dose escalation > 3.5 cm.

### Study treatment and procedures

Patients eligible and willing to participate are randomized to one of two treatment arms – HA-WBRT+SIB vs. WBRT+SIB. The schedule of enrolment, interventions and assessments are provided in Table 1. Each study center is asked to participate in a radiotherapy-planning dummy run before the inclusion of the first trial patient in order to ensure uniformity in image co-registration, contouring and treatment planning.

**Table 1 Tab1:** Flowchart of enrolment, interventions and assessments

	Staging	Therapy		Follow-up				
	T_**0**_	Start	End	T_**1**_	T_**2**_	T_**3**_	T_**4**_	T_**5**_ – T_**x**_
	1 week before RT (day − 6 until day 0)	Day 1 of RT	Day 12 of RT	6 weeks after RT (+/− 7 days)	3 months after RT (+/− 10 days)	9 months after RT (+/− 10 days)	18 months after RT (+/− 10 days)	every 12 months, starting at 30 months after RT (+/− 28 days)
Check of in−/ exclusion criteria	**X**							
Patient information, informed consent	**X**							
Registration	**X**							
Randomization	**X**							
**TREATMENT PLANNING AND IMAGE ACQUISITION**								
Planning of Radiotherapy	**X**							
Upload of planning CT and structure sets	**X**							
Upload of MR images	**X**			**X**	**X**	**X**	**X**	**X**
**DOCUMENTATION**								
Documentation of demographic data and medical history	**X**							
Clinical, neurological examination	**X**	**X**		**X**	**X**	**X**	**X**	**X**
Documentation of medication	**X**	**X**		**X**	**X**	**X**	**X**	**X**
Documentation of adverse events		**X**		**X**	**X**	**X**	**X**	**X**
**ASSESSMENT OF TARGET VARIABLES**								
NCF Assessment (VLMT, WMS-R-Digit Spans, TMT-A /−B)	**X**				**X**	**X**	**X**	**X**
Depression Assessment (HADS-D)	**X**				**X**	**X**	**X**	**X**
QoL Assessment (QLQ-C15-PAL/−BN20, SEIQoL-Q)	**X**				**X**	**X**	**X**	**X**
Study-specific MRI	**X**			**X**	**X**	**X**	**X**	

All patients undergo a planning computed tomography (CT) with 1–2 mm slice thickness in mask immobilization, as well as MRI imaging using a minimum 1.5 Tesla MR-scanner. Minimum MRI requirement is the acquisition of a three dimensional (3D) T1-weighted sequence with 1 mm^3^ large isotropic voxels before and after intravenous application of a Gadolinium-containing contrast medium. The MRI datasets (Gd-T1-MRI) are co-registered on the planning-CT acquired in treatment position. Non-elastic registration has to be performed; non-rigid methods are not allowed. The quality of co-registration is to be checked by the radiation oncologist before target volume contouring by visual inspection of anatomical landmarks in all image modalities for topographical matching.

Gross tumor volume for each metastasis (GTV_met_) is defined as the contrast-enhancing lesion on Gd-T1-MRI. Planning tumor volume for metastases, PTV_met_ is produced as 1 mm 3D margin expansion of the GTV_met_. CTV for whole brain (CTV_WB_) is defined as the whole-brain parenchyma. Planning target volume (PTV) for whole brain in Arm A, PTV_WB-A_, is defined as the CTV_WB_ + 5 mm excluding the PTV_met_ and the hippocampal avoidance regions (HAR). Planning target volume for whole brain in Arm B, PTV_WB-B_, is defined as the CTV_WB_ + 5 mm excluding the PTV_met_. Planning target volume (PTV) for resection cavity, PTV_res_, is defined as the CTV_res_, including the potential GTV of contrast enhancement areas around the resection cavity (tumor rests), + 2 mm. Bilateral hippocampal contours are manually generated on the fused MRI and CT planning image set by physicians according to the contouring atlas for RTOG 0933 (Fig. 1) [18]. HAR is defined as a 7 mm 3D expansion around the hippocampus.

**Fig. 1 Fig1:**
[figure not shown]
Hippocampus contouring (red) according to the contouring atlas for RTOG 0933 [18]

Linear accelerator-based intensity-modulated radiation therapy and volumetric modulated arc therapy techniques or helical tomotherapy are required for planning (Fig. 2).

**Fig. 2 Fig2:**
[figure not shown]
Example of dose distribution and dose-volume histogram of a HA-WBRT+SIB plan in a patient with 7 brain metastases. HAR = hippocampus avoidance region; PTVmet = planning target volume for metastasis (gross tumor volume + 1 mm); PTV Whole brain (whole brain + 5 mm – HAR– PTVmets). Mean dose in the hippocampi under 10 Gy, mean dose for whole brain and metastases 30 and 51 Gy respectively

The prescribed dose is 30Gy in 12 fractions for PTV_WB-A_ or PTV_WB-B_ and 51Gy in 12 fractions (4.25Gy/fraction on 95% of volume) as SIB to individual brain metastases (brain stem metastasis and resection cavities: 42Gy in 12 fractions, 3.5Gy/fraction). In the experimental arm, a simultaneous integrated protection (SIP) to the hippocampi is applied, with a dose in 98% of the volume (D_98%_) ≤ 9Gy and in 2% of the volume (D_2%_) ≤ 17Gy [28]. In the control arm, D_98%_ to the hippocampi must be kept ≥25Gy. A high precision conformal radiotherapy with a steep dose gradient is required. Treatment is to be delivered once daily, with 5 fractions per week. Detailed information on the applied dose and on constraints for organs at risk can be seen in Tables 2, 3, 4.

**Table 2 Tab2:** Treatment planning (PTV_WB-A_ = Planning target volume of the whole brain in arm A, PTV_WB-B_ = Planning target volume of the whole brain in arm B, PTV_met_ = Planning target volume of metastases)

Radiation treatment planning	PTV_**WB- A or -B**_	PTV_**met**_	Major deviations
Prescribed total dose to PTV	30 Gy	51Gy (brain stem metastasis and resection cavity: 42Gy)	< or > 30Gy for PTV_WB-A or -B_ < or > 51Gy for PTV_met_ (brain stem metastasis and resection cavity: < or > 42Gy)
Prescribed dose per fraction in PTV	2.5 Gy	4.25Gy (brain stem metastasis and resection cavity: 3.5Gy)	< or > 2.5Gy for PTV_WB-A or -B_ < or > 4.25Gy for PTV_met_ (brain stem metastasis and resection cavity: 3.5Gy)
Number of fractions per day	1	1	> 1
Treatment duration	12 days 5 days/week	12 days 5 days/week	< or > 12 days < 4 or > 5 days/week

**Table 3 Tab3:** Planning target volume (PTV) – specifications for total dose (PTV_WB-A_ = Planning target volume of the whole brain in arm A, PTV_WB-B_ = Planning target volume of the whole brain in arm B, PTV_met_ = Planning target volume of metastases, PTV_res_ = Planning target volume of resection cavity)

Parameter	Per Protocol	Minor Deviation	Major Deviation
PTV_WB-A or -B_	D_98%_ ≥ 25Gy D_mean_ ≤ 35 Gy	24Gy ≤ D_98%_ < 25Gy 35Gy < D_mean_ ≤ 37 Gy	D_98%_ < 24Gy D_mean_ > 37 Gy
PTV_met 51Gy (brain metastases)_	D_98%_ ≥ 48.4Gy D_2%_ ≤ 63.7Gy	47.4Gy ≤ D_98%_ < 48.4Gy 63.7Gy < D_2%_ ≤ 66.3Gy	D_98%_ < 47.4Gy D_2%_ > 66.3Gy
PTV_met 42Gy_ (brain stem metastases) PTV_res 42Gy_	D_98%_ ≥ 39.9Gy D_2%_ ≤ 52.5 Gy	39.06 Gy ≤ D_98%_ < 39.9Gy 52.5 Gy < D_2%_ ≤ 54.6 Gy	D_98%_ < 39.06 D_2%_ > 54.6 Gy

**PTV*_*WB-A*_

**Table 4 Tab4:** Organs at risk (OAR)

Parameter	Per Protocol	Minor Deviation	Major Deviation
Hippocampus in Treatment Arm A (HA-WBRT+SIB)	D_98%_ ≤ 9Gy D_2%_ ≤ 17Gy	9 Gy < D_98%_ ≤ 10Gy 17Gy < D_2%_ ≤ 18Gy	D_98%_ > 10Gy D_2%_ > 18Gy
Hippocampus in Treatment Arm B (WBRT+SIB)	D_98%_ ≥ 25Gy	24Gy ≤ D_98%_ < 25Gy	D_98%_ < 24Gy
Optical nerves Chiasm	D_2%_ ≤ 33Gy	33Gy < D_2%_ ≤ 35Gy (36Gy^a^)	D_2%_ > 35Gy (36Gy^a^)
Optical nerve, one-sided	D_2%_ ≤ 35Gy	35Gy < D_2%_ ≤ 37Gy	D_2%_ > 37Gy
Retina, one-sided	D_2%_ ≤ 33Gy	33Gy < D_2%_ ≤ 35Gy (49Gy^a^)	D_2%_ > 35Gy (49Gy^a^)
Lenses	D_2%_ ≤ 7Gy	7Gy < D_2%_ ≤ 10Gy	D_2%_ > 10Gy
Inner ear (in case of bilateral involvement)	D_2%_ ≤ 33Gy	33Gy < D_2%_ ≤ 35Gy (36Gy^a^)	D_2%_ > 35Gy (36Gy^a^)
Eyes	D_2%_ ≤ 33Gy	33Gy < D_2%_ ≤ 35Gy	D_2%_ > 35Gy
Brain stem (if metastasis inside the brainstem: brain stem-PTV_met_)	D_2%_ ≤ 33Gy	33Gy < D_2%_ ≤ 35Gy (51Gy^a^)	D_2%_ > 35Gy (51Gy^a^)

^a^in case of brain metastasis in the vicinity of OAR

Investigators enter pseudonymized patient data into electronic case report forms with automatic validation programs checking for completeness, consistency and plausibility. Randomization is performed centrally at the Medical Center – University of Freiburg and stratified by center, in blocks of variable length, based on computer-generated lists. The block lengths are documented separately and are not to be disclosed to the centers. Patients and assessors of NCF and MRI are blinded to treatment assignment. The use of different access rights to the electronic case report forms for treating radiation oncologists and for assessors of NCF and MRI assist in maintaining blinding.

During study treatment, any medication clinically indicated may be applied, with the exceptions of benzodiazepines, barbiturates, topiramate, and hydantoines used as antiepileptic medication. However, in case of an emergency, any medical treatment is allowed. Patients are to be excluded from the study in case of adverse events not allowing continuation of radiotherapy, non-hematological Common Terminology Criteria for Adverse Events (CTCAE) grade 4 toxicity, lack of cooperation, compliance or adherence to protocol, investigator judging the patient risk-benefit ratio to be unfavorable, patient taking drugs not permitted or participating in other trials, and pregnancy. Patients who withdraw from radiotherapy prematurely should still be subject to the same assessments as they would have had if they had completed the study treatment.

### Neurocognitive function assessment

The primary endpoint is the hippocampal-dependent episodic memory after treatment. Differential worsening of the two treatment groups from pre- to post-treatment is to be evaluated. The specific hypothesis to be tested is that 3 months after treatment – compared to pre-treatment – episodic memory decline in the HA-WBRT+SIB group is less severe than in the group of patients who received WBRT+SIB.

The primary endpoint will be assessed with the German version of the Auditory Verbal Learning Test [29], the VLMT (*Verbaler Lern- und Merkfähigkeitstest*) [30]. The VLMT is a standardized test with proven sensitivity to hippocampal dysfunction [31] and association with memory-related hippocampal activation [32]. Feasibility and adequacy of using the VLMT in similar settings have been demonstrated. Comparing two groups of patients with temporal lobe resections either including or sparing the hippocampus, Wagner et al. found that the patients whose hippocampus had been resected showed a significantly stronger decline of verbal learning performance after surgery as assessed with the VLMT [33]. The VLMT has also been used before in studies investigating the effects of WBRT for brain metastases [6] and chemotherapy for central nervous system lymphoma [34].

Among the secondary endpoints, episodic verbal memory and changes in delayed recall are assessed with the VLMT at additional time points: 9 and 18 months after treatment, in order to investigate acute and long-term effects of WBRT and the benefits of HA. Beyond 18 months after the end of WBRT, all patients who are still alive receive NCF assessment with VLMT once per year.

Episodic memory is a higher cognitive function that depends on basal cognitive processes like perception and attention and is also impaired by decreased information processing speed. Therefore, in the current study, short term and working memory, as well as information processing speed and cognitive flexibility are tested. Verbal short term and working memory performance are assessed with the subtests ‘Digit Span Forward’ and ‘Digit Span Backward’ from the German version of the WMS-R (Wechsler Memory Scale-Revised) [35], while information processing speed, visuo-motor tracking abilities as well as executive functions with the TMT (Trail Making Test) [36]. The ‘Digit Spans’ subtest and the TMT are applied among the secondary endpoints before and 3, 9, and 18 months after treatment. Beyond 18 months after the end of WBRT, all patients who are still alive are tested once per year.

NCF assessments are performed or supervised by experienced neuropsychologists in order to ensure standardization and comparability of results. A good compliance of patients treated for brain metastases has been demonstrated in a similar setting, even with a more extensive test battery [23].

### Assessment of depression

Depression can have a negative impact on memory performance [37, 38] and is frequent in patients treated with radiotherapy [39]. In order to account for effects of depression on the primary outcome variable, the German version of the Hospital Anxiety and Depression Scale (HADS-D) [40] is used. The baseline and depression score at 3 months are to be used for adjustment in a sensitivity analysis of the treatment effect on the primary endpoint memory performance.

Evaluation of depression is performed before, as well as 3, 9, and 18 months after treatment. Beyond 18 months after the end of WBRT, all patients who are still alive receive evaluation of depression once per year. The change in the depression sum score from pre- to post-treatment time points is to be analyzed.

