### Statistical planning and analysis

The sample size calculation is based on the primary outcome, which is defined as the difference between the learning scale of the VLMT (word count, 0–75 words) in survivors at 3 months after radiation therapy and at baseline.

Assuming a mean decline after WBRT+SIB of 15 words in VLMT and a common standard deviation of 15 words [6], the study is planned to reject the null-hypothesis of equality of treatment arms with 80% power on the basis of a two-sample t-test at a one-sided significance level of 10% if the deterioration of NCF improves to a 7 words decline after HA-WBRT+SIB. Under these assumptions, 66 patients are required for analysis. According to the patients’ prognosis, we expect about 55% of patients in both arms to survive until 3 months after radiation, plus some additional drop-out of patients unwilling or unable to perform the test. We reckon that 50% of randomized patients will be available for analysis. Therefore, 132 patients should be randomized.

In the primary analysis, differences between HA-WBRT+SIB and WBRT+SIB with respect to the primary endpoint will be estimated and tested within a linear regression model in patients who survive until 3 months after radiation therapy. The model will include treatment and study center as independent variables and will adjust for the baseline learning scale word count of the VLMT. In case of endpoint values missing for reasons other than patient death, these will be handled by multiple imputation. The primary analysis population is the per-protocol set, defined as the group of randomized patients who had no major violations of eligibility criteria and who received treatment as per protocol according to their randomized arm. Sensitivity analyses of the primary endpoint as pre-defined in the study protocol will be performed.

Descriptive and explorative statistical analyses will be performed with respect to the secondary efficacy endpoints. Overall, PFS rates in the two treatment arms will be estimated by the Kaplan-Meier method, and the corresponding endpoints will be analyzed with the Cox model.

For safety analyses, rates of adverse events and the use of corticosteroids will be calculated with 95% confidence intervals.

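### The planned sensitivity analysis adjusts for 3-month depression, a post-randomisation outcome, so it does not test the total treatment effect if treatment affects mood directly or through memory

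*Protocol article*

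**What the plan says.** The section Assessment of depression gives the purpose of collecting HADS-D: "In order to account for effects of depression on the primary outcome variable". For the primary memory endpoint, it then fixes the analysis: "The baseline and depression score at 3 months are to be used for adjustment in a sensitivity analysis of the treatment effect".

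The timing is explicit: "Evaluation of depression is performed before, as well as 3, 9, and 18 months after treatment". Table 1 places HADS-D and the VLMT together at T2, three months after radiotherapy, which is the primary endpoint visit. The same section also treats depression as an outcome: "The change in the depression sum score from pre- to post-treatment time points is to be analyzed".

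The primary model, under Statistical planning and analysis, contains no post-baseline covariate: "The model will include treatment and study center as independent variables and will adjust for the baseline learning scale word count of the VLMT".

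**The concern.** A sensitivity analysis of a treatment effect should ask the primary question again under different assumptions. The primary model asks for the total effect of hippocampal avoidance on the 3-month change in word count. Adding a variable measured after treatment, at the same visit as the endpoint, can change the question. It becomes whether the arms differ in memory among patients with the same 3-month mood.

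The article's own reasoning makes it plausible that 3-month mood depends on treatment. Background says of memory: "Memory deficits are correlated with and precede decreased quality of life". Quality of life assessment attributes impaired quality of life largely to cognitive dysfunction, expects a smaller decline in the hippocampal-avoidance arm, and uses an instrument with an emotional functioning scale. Assessment of depression adds that depression can impair memory. So mood may be a consequence of the memory effect, or a route by which treatment reaches memory.

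What is at stake is interpretation. A real benefit could shrink in this model and be read as fragile or as explained by depression. The adjusted figure could also be taken as the one corrected for confounding.

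**Working it through.** **1. The planned effect and sample size.** Inputs from Statistical planning and analysis: "Assuming a mean decline after WBRT+SIB of 15 words in VLMT and a common standard deviation of 15 words", a 7-word decline in the experimental arm, one-sided 10% level and 80% power. The planned effect is 15 − 7 = 8 words. The normal approximation gives n per arm = 2(1.2816 + 0.8416)² × 15²/8² = 31.7, so 32. The exact t-test has power 0.799 with 32 per arm and 0.808 with 33 per arm. Hence 33 per arm, 66 analysed, and 66/0.5 = 132 randomised. The stated figures reproduce.

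**2. What adjustment for 3-month depression does.** Let H be the 3-month HADS-D score in within-arm SD units. Let *a* be the arm difference in H (experimental minus control) and *s* the within-arm slope of the memory change on H, in words per SD. Both are taken given the other covariates. For linear regression:

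adjusted effect = total effect − *a* × *s*.

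The two effects agree when *a* = 0, that is, when treatment does not shift 3-month depression by any route, or when *s* = 0.

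**3. Illustration: memory drives mood, with no other effect of treatment on mood.** Let ρ be the size of the within-arm memory–mood correlation. With a memory SD of 15, *a* = −8ρ/15 and *s* = −15ρ, so *a* × *s* = 8ρ² and the adjusted effect is 8(1 − ρ²). The SD cancels. The values of ρ are assumptions; the document gives none.

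| Assumed ρ | 8(1 − ρ²), words | Attenuation |
|---|---|---|
| 0.3 | 8 × 0.91 = 7.28 | 9% |
| 0.4 | 8 × 0.84 = 6.72 | 16% |
| 0.5 | 8 × 0.75 = 6.00 | 25% |

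A simulation with 1,000,000 patients gave 7.26 and 6.05 for ρ = 0.3 and 0.5, in line with the formula.

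**4. Other routes, also on assumed inputs.**
- *Mood as mediator.* Suppose treatment lowers H by 0.2 to 0.5 SD and each SD of depression costs 2 to 5 words. The adjusted effect runs from 8 − 0.2 × 2 = 7.6 to 8 − 0.5 × 5 = 5.5 words.
- *Unmeasured common cause of mood and memory, with treatment also shifting mood.* Suppose depression has no effect on memory, the shift is 0.3 to 0.5 SD, and the common cause has a loading of 0.3 to 0.5 on each variable. The slope is then −15 × loading². The adjusted effect runs from 8 − 0.3 × 15 × 0.09 = 7.6 to 8 − 0.5 × 15 × 0.25 = 6.1 words (simulation: 7.61 and 6.15).
- *The same common cause, but treatment does not shift mood.* Then *a* = 0. The simulation returned 7.99 and 8.03 words, so there is no bias.

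**5. Limits of the figures.** The common-cause range uses the SD of 15 from the sample size calculation. The planned model also adjusts for baseline VLMT, and a smaller residual SD would shrink that bias in words. All scenarios attenuate because *a* and *s* were given the same sign. The document does not fix either sign.

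**The case against.** The strongest reply is that nothing decisive depends on this model. The primary analysis uses treatment, centre and baseline VLMT, and the depression-adjusted figure would stand beside it as support. That is right, and it limits the weight of the point.

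A second reply is that the bias is conditional. A reader might infer that adjusting for a post-randomisation score necessarily removes part of the effect, or that the adjusted coefficient can never estimate it. The document does not support that. It hypothesises no effect of hippocampal avoidance on HADS-D, both arms receive radiotherapy, and patients are blinded. The stated link runs from memory to quality of life, not specifically to depression. A reader might also infer that shared causes of mood and memory are enough to bias the treatment coefficient. They are not: treatment must also shift 3-month depression.

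A third reply is that the question is legitimate. The Discussion wants cognitive change interpreted in the light of anxiety, depression and quality of life, and asking whether a memory difference persists at equal mood is a recognisable direct-effect question. The full protocol, which is not shown, may give the assumptions. This stands as a reason to keep such a model under a proper label. It does not turn it into a sensitivity analysis of the total effect, which is how the article describes it. Even as a direct effect, it needs no unmeasured common causes of mood and memory and no effect of memory on mood; the section states neither condition.

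Finally, part of the remedy is already planned, since the change in depression score will be analysed.

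**Conclusion.** The point holds in conditional form. As described, the model tests the robustness of the total treatment effect only if treatment leaves 3-month depression unchanged, both directly and through memory. The article's reasoning about memory and quality of life makes the opposite plausible without establishing it. If treatment does shift mood, the adjusted coefficient answers a different question, may be attenuated, and is distorted further by any unmeasured common causes.

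The size is not computable from the document. The illustration of 7.3 to 6.0 words in place of 8 rests on assumed correlations of 0.3 to 0.5 with memory driving mood. It is not a forecast. The primary analysis, its test and the sample size of 66 and 132 are unaffected, so a reader should not infer that the trial's main conclusion is threatened.

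**What to change.** In Assessment of depression, and wherever the sensitivity analyses are specified:

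- Adjust the sensitivity analysis of the treatment effect for baseline HADS-D only. This deals with chance imbalance in mood before treatment and leaves the target of the primary model unchanged.
- Keep the planned analysis of HADS-D change and report it by arm as an outcome, so that readers can see whether 3-month mood differs between arms.
- If a model with the 3-month score is wanted, present it as an exploratory mediation (direct-effect) analysis. State its assumptions: no unmeasured common causes of mood and memory, and no effect of memory on mood.

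The cost is a change of one or two sentences. No data collection, sample size or primary analysis changes.
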